### Data monitoring

In accordance with ICH-GCP guidelines, the DFEND investigators will support regular trial-related monitoring and quality assurance audits by providing direct access to source data documents. King’s Health Partners Clinical Trials Office will monitor the study at all sites. All research staff will be advised to ensure that a thorough audit trail is maintained throughout the trial.

### Oversight committees

Regular meetings will take place with the data monitoring committee, comprising an independent chair, an independent statistician and an independent psychiatrist. This committee will safeguard the interests of DFEND trial participants, periodically review and evaluate the safety of the interventions during the trial, monitor the overall conduct of the trial and make recommendations to the trial steering committee (TSC) concerning the continuation, modification or termination of the trial. The data monitoring committee will also advise the chief investigator and trial management group to protect the validity and credibility of the DFEND trial.

The TSC has four independent members: two independent psychiatrists (one acting as chair) and two patient-and-public representatives. In addition, the DFEND chief investigator and a co-investigator sit on it. The TSC provides overall supervision of the trial, reporting on behalf of the sponsor and funder. The TSC ensures that the trial runs according to rigorous standards by monitoring the safety of participants, the progress of the trial, protocol adherence, patient safety and relevant information that could impact the trial aims. The TSC also advises the investigators on all aspects of the trial.

### Safety monitoring

An adverse event is defined as any untoward medical occurrence in a subject to whom a medicinal product has been administered, including occurrences that are not necessarily caused by or related to that product. Any adverse event that occurs between the time of consent to the study through to 28 days following the last dosing visit will be recorded. The principal investigators and study doctors will assess whether the adverse event may be related to the study intervention.

Serious adverse events, serious adverse reactions and unexpected serious adverse reactions are defined as any adverse event, adverse reaction or unexpected adverse reaction, respectively, that results in death, is life-threatening, requires hospitalisation or prolongation of existing hospitalisation, results in persistent or significant disability or incapacity, or results in a congenital anomaly or birth defect. All serious adverse events will be reported for this trial except hospitalisations due to a deterioration in mental state, as we anticipate a high proportion of our participants will be hospitalised for this reason during the trial. All hospitalisations or contact with home treatment teams will be recorded, for example on a service contact form.

In addition, the following assessments will be used to determine subject safety during the study at 3 and 6 months:
Corrected serum calcium levels (Ca^2+^) will be tested at baseline, at 3 and 6 months, and more frequently if nausea or vomiting occur.At 3 and 6 months, a parathyroid hormone test will be performed on the blood sample if the corrected Ca ^2+^ level is above the normal range. If participants report nausea or vomiting between visits, they will be advised to contact their doctor for a Ca^2+^ blood test.At baseline, female participants will undergo a urine dipstick pregnancy test (testing for beta human chorionic gonadotropin). Female participants of child-bearing age who refuse to take a pregnancy test at baseline will be excluded from participating in the trial. At each treatment visit (monthly for 6 months), the test will be performed again to determine pregnancy status. Pregnancy tests will not be undertaken by female participants who are permanently sterile or who are post-menopausal (no menses for 12 months without an alternative medical cause). If the urine test is positive, the participant will be withdrawn from the trial medication but encouraged to remain in the study. In the event that it is not possible to obtain a urine sample, a blood sample will be obtained and tested for beta human chorionic gonadotropin. No dose of IMP will be administered to female participants without first checking their pregnancy status (except for patients who are permanently sterile or post-menopausal, as described above).

Discontinuation of treatment will occur if a participant begins taking vitamin D doses above 400 IU per day, if they become pregnant, if their parathyroid hormone test is abnormal or at the discretion of the principal investigator.

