### Participant timeline

Following consent and confirmation of eligibility, participants will be randomised to their treatment allocation within 14 days of the baseline assessment. They will attend 6 monthly visits to receive the dose of IMP or placebo. Final outcome measures will be assessed at the Month 6 visit. Each patient will receive a telephone call 28 days after their last dose of IMP/placebo as part of the close-out. The end of the trial will be defined as the last patient last close-out (Fig. 2).

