### Intervention

All eligible patients will be randomised to receive once per month either 120,000 IU of vitamin D_3_ (cholecalciferol) (equivalent to 4000 IU per day) or placebo for a maximum of 6 months in a 1:1 ratio. We selected monthly dosing to help with adherence because this clinical group may already have a high tablet burden and are routinely assessed at intervals.

Vitamin D will be given as the drug Vigantol®, which contains vitamin D_3_ (cholecalciferol) in oil. The placebo will be an organoleptically matched triglyceride oil (Miglyol® 812 oil). Both the active medication and the placebo will be packaged in identical sealed glass bottles (fill volume of 8 mL). They will be administered orally as a 6 mL dose given in a graduated oral syringe by a trained researcher. Participants will receive a dose of either active medication or placebo at each monthtly visit over 6 months for a total of six doses. 

Guy’s and St Thomas’ Pharmacy Manufacturing Unit (London, UK) is responsible for arranging the manufacture of the investigational medicinal product (IMP), randomised labelling, packaging and final release by a qualified person for clinical trial use.

No restrictions are placed on prior or concomitant interventions (medications or therapies, rescue or subsequent treatments), other than that we ask the participants to refrain from taking vitamin D supplements (including multivitamins that contain vitamin D) that exceed 400 IU/day for the duration of the trial. This will be checked at baseline and each monthly visit.

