### Assignment of intervention

Each bottle of IMP, whether the active medication or placebo, has a unique identification number. Each participant is assigned a unique identification number, which will be used throughout the duration of their treatment. When a participant’s identification number is entered into the randomization system, the algorithm will randomly allocate them to a study arm and notify the unblinded members of staff. At each monthly visit, pharmacy staff will assign a specific bottle of IMP to the participant. Only pharmacy staff dispensing the IMP and the pharmacy monitor (a clinical research associate) will be unblinded. The blinded members of staff include all research team members at site level including the chief investigator, each study site’s principal investigator, researchers undertaking assessments at each time point and trial statisticians. Participants will remain in their allocated treatment arm for the duration of the study, even if they discontinue taking their IMP.

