### Statistical analysis

Full details of the statistical analyses will be specified in a statistical analysis plan written in collaboration with the trial statisticians.

Descriptive analyses, recruitment rate, consent rate, loss to follow-up, departures from randomised treatment and the prevalence of serious adverse events post-randomisation will be reported and summarised by treatment arm over the course of the study. All causes of withdrawal from the randomised treatment will be reported.

Analyses will be carried out by the trial statistician, who will remain blinded until all analyses are completed. The analysis of vitamin D concentrations in blood samples taken at 6 months, which is a secondary outcome, will be carried out after all other analyses are completed, as there is a high expectation that the mean concentration will be higher in the intervention group.

An intention-to-treat analysis of the effect of vitamin D supplementation on the primary PANSS outcome will be conducted using linear mixed modelling. All the available follow-up data from the randomised participants will be modelled. The analysis model will include treatment arm (vitamin D or placebo), time (3 or 6 months), baseline PANSS and randomisation stratifier (ethnicity) as explanatory variables. The model will also contain a subject-varying random intercept to account for any correlation between the repeated measures. Treatment effects on the other secondary outcomes at 6 months will be assessed using similar modelling techniques, employing generalisations to non-normal data where necessary.

To address the secondary research objectives, we will also estimate treatment effects for the subpopulation who were vitamin D insufficient at baseline in terms of primary and secondary outcomes, except for 25OHD blood concentrations, by including relevant interaction terms between baseline vitamin D insufficiency status and treatment group in the statistical models.

We expect that some data will be missing in the post-treatment outcome variables. The linear mixed modelling analyses are based on maximum likelihood and will provide valid inferences under a missing-at-random missingness mechanism. We will explore predictors of missingness. If deemed suitable for adjustment, we will include these as explanatory variables in the analyses. If post-randomisation variables are identified, a multiple imputation model will be considered instead [49].

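### As written, adverse event recording ends 28 days after the last dose, so participants who stop treatment early but stay in follow-up can lose up to about five months of event capture before Month 6

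*Protocol article*

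**What the plan says.** Five statements in the protocol article bear on this.

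- **Recording window** (Safety monitoring): adverse events count from consent "through to 28 days following the last dosing visit will be recorded".
- **Close-out** (Participant timeline): "Each patient will receive a telephone call 28 days after their last dose of IMP/placebo as part of the close-out". This is tied to the individual's exposure, not to a calendar point.
- **Staying in after stopping** (Assignment of intervention): "Participants will remain in their allocated treatment arm for the duration of the study, even if they discontinue taking their IMP". For a positive pregnancy test, Safety monitoring adds that "the participant will be withdrawn from the trial medication but encouraged to remain in the study". Other listed reasons for stopping are an abnormal parathyroid hormone result, non-study vitamin D above the permitted amount, and the investigator's decision.
- **End of follow-up** (Participant timeline): "Final outcome measures will be assessed at the Month 6 visit".
- **Reporting** (Statistical analysis): "the prevalence of serious adverse events post-randomisation will be reported and summarised by treatment arm over the course of the study".

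Dosing is described as "They will attend 6 monthly visits to receive the dose of IMP or placebo" and, under Intervention, "over 6 months for a total of six doses". The text does not say whether those doses fall at months 0 to 5 or months 1 to 6. The schedule is in Fig. 1, which is not available here.

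**The concern.** The recording window follows exposure, while retention and the serious adverse event summary follow the study. The two periods separate for anyone who stops the product and is still followed. That person goes on contributing outcome data, but under the stated rule their adverse events cease to be recorded 28 days after the last dose.

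The loss may not be random with respect to harm. One listed reason for stopping, an abnormal parathyroid hormone test, is itself a safety signal: at 3 and 6 months the test is run only when corrected calcium is above normal. If such stops are more frequent in one arm, that arm has less observed time in precisely the participants in whom later events matter most, and a by-arm table would not show it.

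**Working it through.** The plan has no derived figure to reproduce; the only stated quantity is the 28 days.

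**Inputs.** From the document: a 28-day window, six monthly doses, final assessment at Month 6, and a minimum of 24 days between doses (Table 1, version 9.1). Assumed: first dose on day 0 and a calendar month of 365.25 / 12 = 30.44 days, so Month 6 is day 6 × 30.44 = 182.6. *Last dosing visit* is read as the participant's own last dose.

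**Formulae.** For a participant who takes k doses at spacing s:

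- window closes on day (k − 1) × s + 28
- uncovered days = Month 6 day − closing day

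**Calendar-month spacing**

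| Doses taken | Last dose (day) | Window closes (day) | Uncovered days before Month 6 |
|---|---|---|---|
| 1 | 0 | 28.0 | 154.6 |
| 2 | 30.4 | 58.4 | 124.2 |
| 3 | 60.9 | 88.9 | 93.8 |
| 4 | 91.3 | 119.3 | 63.3 |
| 5 | 121.8 | 149.8 | 32.9 |
| 6 | 152.2 | 180.2 | 2.4 |

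After one dose, 28 / 182.6 = 15% of follow-up is covered; after three, 88.9 / 182.6 = 49%.

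**Sensitivity to the schedule (uncovered days)**

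| Schedule | 1 dose | 3 doses | 6 doses |
|---|---|---|---|
| 30-day spacing, Month 6 = day 180 | 152 | 92 | 2 |
| 28-day spacing, Month 6 = day 168 | 140 | 84 | 0 |
| 24-day spacing, Month 6 = six intervals (day 144) | 116 | 68 | −4 |
| 24-day spacing, Month 6 fixed at day 182.6 | 154.6 | 106.6 | 34.6 |
| Calendar doses at months 1 to 6 | 124.2 | 63.3 | −28 |

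In the last row each dose falls one month later, so k doses close the window at k × 30.44 + 28: day 58.4 after one dose, day 119.3 after three and day 210.6 after six. A negative value means the window closes after Month 6.

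The gap after one or three doses is present under every schedule. The gap after six doses is about 2 days, nil or reversed, except when the minimum interval is used at every visit and Month 6 is held to the calendar.

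**The safety-prompted stop.** The fixed post-baseline calcium test before the final one is at Month 3. A stop on its result would leave three or four doses taken (calendar doses from day 0), hence about 94 or 63 uncovered days. Earlier stops are possible, because the Fig. 1 legend allows calcium and parathyroid hormone testing at any monthly visit when nausea or vomiting is reported.

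**The case against.** Four objections have weight.

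1. **Wording.** Safety monitoring speaks of a dosing visit, whereas Participant timeline speaks of a dose. If the last *scheduled* dosing visit is meant, the early-stopper gap largely disappears: with a sixth visit at month 5, the window would close near day 180 for everyone. This cannot be excluded, but the article does not say so, and the close-out wording points to the individual's last dose.

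2. **Serious events may be protected.** The same section says all serious adverse events are reported, apart from admissions for worsening mental state, and gives no separate time limit. All hospitalisations and home treatment contacts are recorded with no end tied to dosing. This stands in part and is why the loss is clearer for non-serious events. It is not a full answer: serious events are defined as a subset of adverse events, and a hospitalisation record would not capture serious events without admission.

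3. **Convention and condensation.** A window of last dose plus 28 days is a common and legitimate choice, and Table 1 notes that version 10.1 clarified the collection of adverse event details. The full protocol may resolve the matter. The point here is not an omitted detail, however: the article states a window, and that window does not fit its own retention and reporting statements.

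4. **Limited evidence of bias.** Pregnancy is not a sign of treatment harm and gives no stated reason to differ by arm. Only the parathyroid hormone criterion is clearly a harm signal, and its fixed route makes the one-dose figure a worst case.

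A reader might also infer that recording closes before Month 6 for everyone. The documents do not support that: the dosing days are not shown, and the 35-day gap for a full course needs an extreme combination of assumptions. Nor is the Month 6 calcium result lost, since it is a scheduled assessment in its own right.

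**Conclusion.** The point holds for participants who stop treatment early and remain in follow-up. As written, their adverse event recording ends before Month 6, by about 155 days after one dose and 94 days after three with calendar-month dosing from day 0. Other plausible schedules give 116 to 155 days and 63 to 107 days. This does not match a summary of serious events by arm for the whole study, and it may under-record events after a stop prompted by safety.

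The conclusion rests on reading the last dosing visit as the participant's own. The number of people affected, and hence the size of any bias, cannot be derived: no treatment-stopping rate is given, and the 20% attrition under Sample size is loss to follow-up.

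Two stronger inferences are not supported. The article promises to report and summarise serious events by arm, not to test a difference. It also does not state that the safety denominator is all randomised participants; intention to treat is specified for the PANSS analysis. The matter should be corrected, but it does not threaten the primary analysis.

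**What to change.** Reconcile Participant timeline, Assignment of intervention, Statistical analysis and Safety monitoring:

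- Define the last dosing visit explicitly.
- Record adverse events for all retained participants, including those who have stopped treatment, from consent to the later of the Month 6 visit and 28 days after the last dose.
- Set the close-out contact, and hence the end of trial, on the same basis.
- Report events by arm over that common period, with an on-treatment table (to last dose plus 28 days) as a supplement.

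Recruitment closed in June 2019 and follow-up was due to end in December 2019, so part of the remedy now lies in reporting. If late events were not collected, give observation time for adverse events by arm, with the number who stopped early and why, and state that the window was limited.

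The cost is small: a wording change and some extra entries, largely at visits and contacts that already take place. The downside is a few more unrelated late events to process.

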### Dissemination

The research findings will be disseminated via peer-reviewed journals, conferences, internal reports and user group meetings and informed by the lived experience of our experts. When the project is complete, we will be able to provide all participants with a general summary of our research through a project newsletter.

## Discussion

There is a growing body of evidence that suggests vitamin D is neuroprotective [1, 2, 10] and that vitamin D deficiency is prevalent in those with schizophrenia [12, 16]. Longitudinally, the severity of symptoms in psychosis has also been associated with vitamin D concentration [24]. Lack of vitamin D is also associated with physical health problems, including adverse cardiovascular outcomes [50], and so may potentially compound the poor health status associated with psychotic disorders [51, 52]. Few studies have, however, examined whether vitamin D supplementation may improve outcomes among people with psychosis. Our study is the first rigorously designed trial to investigate the impact of vitamin D supplementation in early psychosis.

Our eligibility criteria include only patients who have the capacity to consent to the trial and thus, who have stable and minimal symptoms. We hypothesise that this will minimise the acute effect of the standard treatment on our outcome measures. We have elected not to restrict eligibility to people known to be vitamin D deficient, as it is not standard practice to test vitamin D levels on first presentation with psychosis. Introducing testing prior to study entry would alter clinical practice and introduce a novel clinical question on how to respond to the findings in the absence of applicable evidence. It would also limit the capacity of the study to determine whether there is benefit in supplementing all people with FEP with vitamin D. As we will be analysing baseline vitamin D levels after trial completion, we will be able to conduct a sub-analysis of this patient group.

A key strength of our study is its methodological rigour, since utilising a double-blind randomised controlled trial design removes potential biases inherent in cross-sectional research. The study is designed to take a practical approach and recruit from local clinics. This approach not only enhances the ecological validity of the outcomes but also augments existing connections between clinical and academic networks.

Vitamin D supplementation after FEP is as yet an unexplored area of research and clinical equipoise exists regarding its potential for benefit [53]. This trial will evaluate whether vitamin D may improve mental health indicators in patients with FEP, with a view to informing protocols for vitamin D in patients with FEP. Vitamin D supplementation is cheap, simple to access (e.g. over the counter), relatively safe and likely to be publicly acceptable [54]. Thus, even if vitamin D shows only small effects on clinical outcomes, vitamin D supplementation may offer a potentially effective treatment avenue for FEP patients.

### Trial status

The current protocol is version 10.1 (3 May 2019). The study protocol was written in accordance with the Standard Protocol Items: Recommendations for Interventional Trials (SPIRIT) guidelines. Table 1 lists the changes to the registered protocol (ISRCTN12424842). The study began recruiting in January 2016, and recruitment was completed on 14 June 2019. Follow-ups will continue until December 2019 and the results are expected to be available in 2020.

**Table 1 Tab1:** Changes to the registered protocol

Protocol version	Description
2	Addition of new questionnaires including on level of sun exposure, frequency of eating food containing vitamin D, key service contacts, Fitzpatrick skin type, levels of physical activity (IPAQ) and duration of untreated psychosis.
3	Addition of second questionnaire assessing physical activity (SIMPAQ). Addition of PANSS assessment at month 3.
4	Changes to all study documents for clarification and to include site-specific information and logos.
5	The definition of the first episode of psychosis was changed from “6 months post-first presentation to services” to “3 years post-first presentation to services”.
6	Change in inclusion criteria to allow patients to take up to 400 IU per day of vitamin D in view of new Public Health England recommendations.
7	Change to inclusion criteria to allow patients aged up to 65 years to participate. Removal of anticonvulsants as an exclusion criterion. Remove hospitalisation due to a deterioration in mental health from the definition of a serious adverse event. Blood test for beta human chorionic gonadotropin was included if a urine test was not possible. Clarification for permitted dosing windows. Total study duration was reduced from 12 to 6 months.
8	Removal of exclusion criteria regarding anaemia, sickle cell anaemia and thalassemia.
9.1*	Clarification of outcome measures. Time between doses to be a minimum of 24 days. Clarification of window for collection of final assessment. Pregnancy test not required if participant is medically sterile or post-menopause. Vitamin D levels will be sent to GP at the end of the study. Phase II designation (not Phase IV).
9.2	Change in study end date to December 2019.
10.1*	Discontinuation of RNA sample collection. Increase in participant reimbursement. Clarifications to existing procedures regarding safety of the iPTH test, service contact form use, collection of adverse event details and attempts to contact participants for the follow-up.

*Protocol versions 9 and 10 were resubmitted as versions 9.1 and 10.1, respectively, after addressing comments from the MHRA and resubmitting to the research ethics committee.

*IPAQ* International Physical Activity Questionnaire, *PANSS* Positive and Negative Symptom Scale, *SIMPAQ* Simple Physical Activity Questionnaire

